# Comparison of the therapeutic effects of 15 mg and 30 mg initial dosage of prednisolone daily in patients with subacute thyroiditis: protocol for a multicenter, randomized, open, parallel control study

**DOI:** 10.1186/s13063-020-04337-8

**Published:** 2020-05-24

**Keywords:** Subacute thyroiditis, Prednisolone, Randomized controlled trial, Chinese population

## Abstract

**Background:**

Subacute thyroiditis (SAT) is the most common cause of thyroid pain. Several clinical guidelines recommend that patients who fail to respond to full doses of non-steroidal anti-inflammatory drugs (NSAIDs) should be treated instead with oral corticosteroid therapy. However, albeit strong recommendations, the treatment protocol is based on low-quality evidence and high-quality clinical trials are lacking with respect to the optimal initiation dosage and usage of corticosteroid. We aimed to evaluate whether 15 mg/day of prednisolone (PSL) as the initial dosage could provide non-inferiority effectiveness but with lower risk and more safety compared with 30 mg/day of PSL as the initial dosage.

**Methods/design:**

This is a multicenter, open-label, randomized, parallel trial that will be conducted at five academic hospitals in China. A total of 90 adult patients diagnosed with SAT who present moderate to severe pain or fail to respond to full doses of NSAIDs will be randomly assigned with a 1:1 ratio to the low initial PSL dosage group (15 mg daily) and standard initial PSL dosage group (30 mg daily). The primary endpoint is the time period (days) required for PSL treatment (including PSL treatment for recurrence).

**Discussion:**

Our randomized controlled trial will try to determine the optimal protocol in the treatment of SAT by providing high-quality evidence.

**Trials registration:**

Chinese Clinical Trial Register, ChiCTR1900023884. Registered on 15 June 2019.

## Background

Subacute thyroiditis (SAT), also named subacute granulomatous or subacute painful thyroiditis or de Quervain thyroiditis, is a transient inflammatory thyroid disease [1]. SAT is the most common painful thyroid disease and the prevalence of SAT is nearly 5% in the population with abnormal thyroid function [2]. According to the data from the Rochester Epidemiology Project in Olmsted County, Minnesota, the incidence of SAT was reported as 12.1 cases per 100,000/year with a higher incidence in females than in males (19.1 and 4.1 per 100,000/year, respectively) [3, 4]. Over 95% of people with SAT often present with moderate-to-severe pain [3], which may be limited to the region of thyroid or radiate to the upper neck, jaw, throat, upper chest, or ears. The pain may begin focally and spread from one side to the other of the gland over several weeks. Patients may also have fever, fatigue, malaise, anorexia, and myalgia.

SAT is a self-limiting disease and the primary treatment is to relieve thyroid pain. Several clinical guidelines, such as the American Thyroid Association (ATA) [5] and the Chinese Endocrinology Association [6], recommend anti-inflammatory agents based on the severity of symptoms. Non-steroidal anti-inflammatory drugs (NSAIDs) are initially used, particularly for mild cases. Oral glucocorticoids (prednisolone [PSL]) are suggested when patients fail to respond, or present initially with moderate to severe pain and/or thyrotoxic symptoms. ATA and UpToDate Clinical Consultants recommend that patients who fail to respond to full doses of NSAIDs over several days (2–3 days) should be treated instead with oral corticosteroid therapy. PSL of 40 mg daily for 1–2 weeks followed by a gradual taper over 2–4 weeks or longer is the most popular recommendation [5]. According to the Chinese Endocrinology Association, the initial PSL dosage of 20–40 mg daily is recommended [6].

However, albeit strong recommendations, the treatment protocol is based on low-quality evidence [3, 7–11] and high-quality clinical trials are lacking with respect to the optimal initiation dosage and usage of corticosteroids. Considering the short- and long-term adverse effects on many organ systems and that the risk is both dose- and duration-dependent [12–16], it is essential to consider the possibility of starting with a minimal dosage of corticosteroid and stop for a short duration. A recent observational study showed that the treatment protocol of PSL 15 mg daily as the initial dosage with tapering by 5 mg every 2 weeks was effective and safe for Japanese patients [17]. In addition, a retrospective study found that PSL treatment with mean dose of 15.0 mg/day (range = 14–16 mg/day) was superior to NSAIDs with regard to resolution of symptoms [18]. Based on the findings, we hypothesized that a low initial dosage of PSL seemed effective in the treatment of SAT; unfortunately there was a lack of high-quality well-designed clinical trials.

Therefore, in the present randomized controlled trial (RCT), we will use 15 mg/day of PSL as the initial dosage for treatment in patients with SAT who fail to respond to full doses of NSAIDs or present initially with moderate to severe pain, with the aim of evaluating whether 15 mg/day of PSL could provide non-inferiority effectiveness but with lower risk and more safety compared with 30 mg/day of PSL.

## Methods

### Study design

This is a multicenter, open-label, randomized, parallel non-inferiority trial. The study will be conducted at five academic hospitals in China: (1) Xiangyang Central Hospital, Affiliated Hospital of Hubei University of Arts and Science; (2) No. 1 Hospital of Yulin; (3) 3201 Hospital of Xi’an Jiao tong University Health Science Center; (4) Tangdu Hospital, Air Force Medical University; and (5) The Second Affiliated Hospital of Xi’an Jiaotong University.

Participants who fulfill the eligibility criteria will be randomly assigned with a 1:1 ratio to any of the following two groups: group 1 = low initial PSL dosage; and group 2 = standard initial PSL dosage. In group 1, 15 mg daily of PSL as the initial dosage for 14 days will be used, followed by a gradual taper by 5 mg every 7–14 days. In group 2, 30 mg daily of PSL as the initial dosage for 5–14 days will be used, followed by a gradual taper of 5–10 mg every 5–7 days (Figure 1).

**Fig. 1 Fig1:**
[figure not shown]
Study flow chart. SAT subacute thyroiditis, PSL prednisolone

### Study population

Individuals should fulfil the following criteria:
Age ≥ 18 years at screening;Diagnosis of SAT and presenting with moderate to severe pain (sore > 7/10) or failing to respond to full doses of NSAIDs;Provide informed consent before any study-specific procedures and not involved in another clinical study in the previous 3 months.

### Exclusion criteria

Individuals should not enter the study if any of the following exclusion criteria are fulfilled:
Women who are pregnant, intending to become pregnant during the study period, currently lactating women, or women of childbearing potential not using highly effective, medically approved methods of birth control;Suspicion or diagnosis of acute suppurative thyroiditis, Graves’ disease, Hashimoto thyroiditis, or thyroid carcinoma;Glucocorticoids allergy or intolerance (e.g. systemic allergic reaction, induced asthma, bleeding, ulcer and perforation of stomach or intestine);Previous treatment with PSLs in the last 6 months before screening;Adrenocortical hyperfunction, uncontrolled hypertension, or diabetes;Patients with clinically apparent liver disease characterized by any of the following:
ALT or AST > 3× upper limit of normal confirmed on two consecutive measurements (by local laboratory) within 4 weeks before the screening period;Impaired excretory (e.g. hyperbilirubinemia) and/or synthetic function, or other conditions of decompensated liver disease such as coagulopathy, hepatic encephalopathy, hypoalbuminemia, ascites, or bleeding from esophageal varices;Acute viral or active autoimmune, alcoholic, or other types of hepatitis.Patients with moderate /severe renal impairment or end-stage renal disease (estimated glomerular filtration rate ≤ 60 mL/min calculated by using the abbreviated equation developed by the Modification of Diet in Renal Disease study with modification for the Chinese population) at screening or within 4 weeks before screening (by local laboratory);Congestive heart failure defined as New York Heart Association class III or IV;Significant cardiovascular history within the past 3 months before screening defined as myocardial infarction, coronary angioplasty or bypass graft(s), valvular disease or repair, unstable angina pectoris, transient ischemic attack, or cerebrovascular accident;History of mental illness;History of corneal ulcer;History of gastrointestinal disease including gastroenterostomy, enterectomy, Roemheld syndrome, severe hernia, and intestinal obstruction;Postoperative patients with unhealing wound;Diagnosed and/or treated malignancy (except for basal cell skin cancer, in situ carcinoma of the cervix, or in situ prostate cancer) within the past 5 years;History of organ transplant or acquired immunodeficiency syndrome;History of alcohol abuse or illegal drug abuse within the past 12 months;Potentially unreliable patients and those judged by the investigator to be unsuitable for the study.

### Randomization methods and concealment mechanism

The stratified block randomization method will be used. Participants will be stratified by research center and the appropriate segment lengths will be selected. Based on the number of seeds, a random coding table of 92 participants will be generated using the statistical software SAS8.2 PROC PLAN. The randomized numbers will be segmented, retained, and managed by the third party who will not be involved in the data collection ([name]). The investigators in research centers will enroll the participants. When needed, the investigators will ask for numbers from the third party by telephone, using the order in which the participants will be treated, and the intervention scheme with that serial number will be provided.

### Methods for ensuring blinding

The aim of the present study is to explore the effects of different dosages of PSL and a definite blindness is deemed worthless for investigators or for the patients. Therefore, an open-label study is conducted in which only laboratory personnel and data analysts (the third party) will be blinded; unblinding will not occur.

### Screening period

In the screening period, patients’ data on demographical information, physical examination, current medical conditions, and history of concomitant diseases will be collected. Laboratory examination including hematology panel, urinalysis, liver function, kidney function, thyroid function, erythrocyte sedimentation rate (ESR) and C-reactive protein (CRP) will be conducted. Thyroid ultrasound and radioactive iodine uptake rate of thyroid (thyroid scintigraphy or fine-needle aspiration cytology as alternatives) will be performed. The thyroid pain will be evaluated based on visual analog scales (VAS) and thyroid tenderness will be categorized by no (–), mild (+), moderate (++), and severe (+++) degrees. Heart rates and temperatures will be monitored. Since eligible patients will be randomized within 1–2 days after screening, laboratory results from the screening period will be considered as baseline data and there will be no need to repeat. However, other data such as thyroid pain, heart rate, and blood pressure should be assessed after randomization and considered as baseline data.

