### Outcomes

The primary endpoint is the time period (days) required for PSL treatment (including PSL treatment for recurrence).

Secondary outcomes include time periods (days) required for complete resolution of thyroid pain (defined as no thyroid pain and no tenderness), time periods required for the relief of thyroid pain (defined as at least 50% decline of VAS scores), percentage of relapse during treatment, and the total dosage of PSL. Safety outcomes include all the AEs, vital signs, and collection of clinical chemistry parameters.

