### Sample size estimate

The present study is a non-inferiority trial. The primary endpoint is the time period (days) required for PSL treatment (including PSL treatment for recurrence). PASS 11.0 software (NCSS, LLC, Kaysville, UT, USA.) was used to estimate sample size.

According to the previous literature [17, 18], the mean time was around 36 days with a standard deviation of 12 days. With a one-sided alpha level of 0.05, group sample sizes of 38 and 38 will achieve the power of 81% to detect non-inferiority with the margin of 7 days and the standard deviation of 12 days. Considering a drop-out rate of 20%, a sample size of 90 patients with a 1:1 allocation rate (45 patients per group) was finally determined.

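### Baseline thyroid pain is recorded after allocation in an open-label trial, so the natural reference for the secondary 50% VAS decline can be influenced by knowledge of the arm

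*Protocol article*

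**What the plan says.** All references are to the protocol article.

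- **Screening period.** Pain is scored before randomisation: "The thyroid pain will be evaluated based on visual analog scales (VAS", with tenderness graded in four categories. On timing, "eligible patients will be randomized within 1–2 days after screening"; Table 1 allows 0 to 3 days. Laboratory results from screening stand as baseline. For the rest the rule differs: "other data such as thyroid pain, heart rate, and blood pressure should be assessed after randomization and considered as baseline data".
- **Table 1.** VAS and tenderness are ticked at both the screening visit and the randomisation visit (visit 2).
- **Randomization methods and concealment mechanism.** The investigator telephones a third party and "the intervention scheme with that serial number will be provided".
- **Methods for ensuring blinding.** "an open-label study is conducted in which only laboratory personnel and data analysts (the third party) will be blinded".
- **Outcomes.** A secondary outcome is "time periods required for the relief of thyroid pain (defined as at least 50% decline of VAS scores". The primary endpoint is different in kind: "The primary endpoint is the time period (days) required for PSL treatment (including PSL treatment for recurrence".

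**The concern.** A baseline value should not depend on the assigned arm. Here the article does not leave the order open: it places the pain baseline after randomisation, and it treats pain differently from the laboratory values, which keep their screening result. VAS pain is self-reported, and an unblinded assessor grades tenderness. A patient who knows the dose, or an investigator who knows it while prompting the score, may produce a different number from the one that would have been given a few minutes earlier.

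The relief outcome is a percentage decline, so the reference value sets the threshold each patient must cross. If the reference shifts differently in the two arms, the thresholds shift differently before any drug has acted. The same value would also enter any table of baseline comparability for pain.

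**Working it through.** **1. Is the chain in the text?** There are four links.
- The value called baseline for pain is taken after randomisation (Screening period): stated.
- The site knows the dose by then (Randomization methods): stated. Patients and investigators are not blinded (Methods for ensuring blinding): stated by exclusion, since only laboratory personnel and analysts are.
- The relief outcome uses a percentage decline (Outcomes): stated. Its reference is not named there, but a percentage decline needs one, and the only pain value the article designates as baseline is the post-randomisation one. This link is the natural reading, not an explicit statement.
- Nothing described withholds the assignment until the score is recorded. The text also does not say whether that score precedes the first dose.

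**2. What depends on it?**
- Primary endpoint (days of PSL): not defined through baseline VAS.
- Complete resolution: an absolute state, with neither pain nor tenderness.
- Relapse percentage and total PSL dosage: no baseline VAS.
- Time to relief: yes.

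**3. Does it touch the sample size?** The plan's own figure reproduces. Inputs from Sample size estimate: margin 7 days, SD 12 days, one-sided alpha 0.05, power 81%.
- n per group = 2 × (1.645 + 0.878)² × 12² / 7² = 37.4, so 38, as stated.
- Power at 38 per group: 7 / (12 × √(2/38)) = 2.543; 2.543 − 1.645 = 0.898; Φ(0.898) = 0.815. With the noncentral t on 74 df it is 0.809.

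No VAS quantity enters, so moving the pain baseline changes neither n nor power.

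**4. Illustration of scale.** The article gives no pain trajectory. Assumptions, not document figures: true baseline B = 8, a shift s in the recorded baseline only, and a linear fall to zero over D days. D = 5 to 10 is the window in which the Treatment period section expects most patients to be pain-free.
- Threshold = (B + s)/2.
- True decline needed = 1 − (B + s)/(2B).
- Time to relief = D × [1 − (B + s)/(2B)].

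| s | Threshold | True decline needed | Time, D = 5 | Time, D = 10 |
|---|---|---|---|---|
| −1 | 3.5 | 56% | 2.81 d | 5.63 d |
| −0.5 | 3.75 | 53% | 2.66 d | 5.31 d |
| 0 | 4.0 | 50% | 2.50 d | 5.00 d |
| +0.5 | 4.25 | 47% | 2.34 d | 4.69 d |
| +1 | 4.5 | 44% | 2.19 d | 4.38 d |

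A 1-point shift moves time to relief by 0.31 day (D = 5) to 0.63 day (D = 10). Under linearity that is 0.5/4 = 12.5% of the unshifted time whatever D is. A half-point shift gives half of this.

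**The case against.** The strongest counter-argument is that every later VAS score is unblinded too. Let knowledge of the arm shift the reported baseline by a and later scores by b. With B = 8, true pain at the moment the threshold is crossed is (8 + a)/2 − b, against a correct value of 4. The error is a/2 − b with a post-allocation reference and −b with a pre-allocation one.
- a = 1, b = 0: error 0.5 point now, none with a pre-allocation reference.
- a = b = 1: error 0.5 point now (true pain 3.5), 1.0 point with a pre-allocation reference (true pain 3).
- Proportional shift of 9/8 = 1.125 throughout: the present rule cancels it exactly (9/2/1.125 = 4). A pre-allocation reference crosses at 4/1.125 = 3.56, an error of 0.44.

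The arithmetic is right, and it shows that protecting the reference need not reduce the total error. It does not rescue the rule. The cancellation needs the reporting shift to persist in the same direction and at a suitable size, which nobody can verify. A pre-allocation reference leaves a single source of error, the one that comes with an open-label design; the present rule adds a second, avoidable one of unknown sign.

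Other objections that stand:
- The shift in the illustration is smaller than the one-day spacing of first-week visits, although it could still move some patients' recorded relief by a whole day.
- Measuring pain again close to the start of treatment is a sensible aim.
- The article does not say that the patient has been told the dose when the visit-2 VAS is taken, only that the site has it and that patients are not blinded.

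**Conclusion.** The point holds in limited form. The rule as written lets the natural reference for one secondary outcome be influenced by knowledge of the arm, and it is worth correcting because the remedy is simple. It rests on reading the post-randomisation score as the reference for the 50% decline.

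A reader might infer more than the document supports:
- **That the main conclusion is at risk.** It is not. The primary endpoint, the sample size and the other three secondary outcomes do not use the value, and the article does not single out time to relief among its secondary outcomes. The three-day rule in Treatment period speaks of significant relief but is not tied to the 50% definition.
- **That time to relief is biased by a known amount or towards a known arm.** The 0.3 to 0.6 day figure depends on an assumed baseline, shift and linear fall, and on later scores being unaffected. Neither size nor direction can be estimated.
- **That a planned adjusted analysis is invalid.** Statistical methods proposes no adjustment for baseline VAS.
- **That a pre-allocation baseline makes the outcome unbiased.** It protects the reference only.

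**What to change.** 1. At visit 2, record VAS and tenderness, with heart rate and blood pressure, before telephoning for the allocation. Table 1 already schedules VAS and tenderness there, so only the order changes. Heart rate and blood pressure feed no efficacy outcome and are included for consistency.
2. State in Outcomes that the 50% decline is measured from a pre-allocation VAS, and amend the Screening period sentence to match.
3. Use one definition for everyone in the relief analysis. Trial status says recruitment began in June 2019, so patients already enrolled under the present rule may have no visit-2 score taken before allocation. Using the screening VAS for them and the visit-2 VAS for later patients would give one outcome two baselines. One workable choice is the screening VAS for all patients, which already exists and precedes allocation, with the visit-2 value as a sensitivity analysis.

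Cost: a reordering of steps, a short amendment, and the need to document a change to an outcome's reference while the trial is running. There is one small statistical downside. The screening VAS is 1 to 2 days older (up to 3 by Table 1), and a score above 7/10 can determine eligibility, so it may regress towards the mean. Because that selection precedes randomisation, the effect is expected to be equal in both arms.

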### Treatment period

Patients who fulfill the eligible criteria will be randomly assigned with a 1:1 ratio to treatment groups and drugs will be dispensed accordingly.

Group 1 is the low initial PSL dosage, in which 15 mg daily of PSL will be provided as the initial dosage for 2 weeks; the dosage will then taper by 5 mg every 7–14 days over 2–4 weeks or longer. Group 2 is the standard initial PSL dosage group, in which 30 mg daily of PSL will be provided as the initial dosage. The dosage will begin to taper 3–7 days after the complete resolve of thyroid pain and then taper by 5–10 mg every 5–7 days over 2–4 weeks or longer. Because most patients will receive complete resolve of thyroid pain within 5–10 days, 30 mg daily of PSL will be provided for around 5–14 days in the standard initial PSL dosage group. However, in the low initial PSL dosage group, 15 mg daily of PSL will be provided for 14 days regardless of the time period of complete pain resolve.

According to the clinical experience and the results of the pre-experiment, the pain of most patients will disappear completely within 5–10 days after receiving PSL treatment, no matter the low initial dose or the standard initial dose. Therefore, if the test group still has pain at 2 weeks, consider termination, adjust to the standard initial dose for treatment and specify the reason (with the exception of the situation that the pain completely disappears but the symptoms recur subsequently). In addition, whether in the low initial dose or in the standard initial dose group, if the pain does not relieve significantly 3 days after PSL is given, it is necessary to re-evaluate the diagnosis of SAT, eliminate other causes (such as acute thyroiditis), and give corresponding treatment if confirmed; if other causes are excluded, the study can be considered to be terminated, and the low initial dose can be adjusted to the standard initial dose for treatment and the reasons recorded in detail; the standard initial dose can be increased to a higher dose (such as 40 mg/day) and the reason specified.

The laboratory parameters that will be measured to assess efficacy and safety at each visit are shown in Table 1. The patients will receive face-to-face daily visit within the first week in research centers; thyroid pain, temperature, and adverse events (AE) will be assessed at each visit. Time periods required for the relief and complete resolution of thyroid pain will be recorded. Blood samples will be taken for the measurement of CRP and ESR in the first week. The patients will then receive telephone visits every 7–10 days. During each telephone visit, thyroid pain, temperature, and AEs will be investigated, medicine usage will be directed and recorded. If patients complain of pain in the tapering period, the tapering of the dosage will be delayed. In some cases with severe pain, the dosage will even increased; the dosage will then be tapered until the thyroid pain disappears. If PSL is tapered to a minimum dosage (i.e. 5 mg) for several days (3–7 days) with no thyroid pain, discontinuation of PSL will be considered and patients will receive a face-to-face visit. During the visit, physical examination (e.g. blood pressure and body weight) will be conducted and a blood sample will be taken for the measurement of thyroid function, liver function, kidney function, glucose level, CRP, and ESR. In addition, AEs will be collected. If SAT recurs after discontinuation of PSL, PSL will be administered again. During the treatment period, anti-ulcer drugs will be administered to some patients with a history of intestinal ulcer or who feel abdominal discomfort during treatment. A hepatologist will be consulted for possible antiviral therapy in patients with inactive hepatitis.

**Table 1 Tab1:** Study plan detailing the procedures

Study period	Screening	Intervention period				
**Visit number**	1	2	3*	4-x	x	x + n
Study interval	– 0–3 days	Randomization	1 week	Every 1 week	PSL discontinuation	Every 4 weeks
Visit window*			(±2 days)	(±2 days)	(±2 days)	(±7 days)
Telephone visit				√		
*Screening/Demography/Baseline*						
Written informed consent	√					
Inclusion / Exclusion criteria	√	√				
Demographics	√					
Physical examination, height, and weight	√					
Medical / Current conditions	√					
History of diabetes and complications	√					
*Intervention*						
Instruction of drugs		√	√	√	√	√
Thyroid pain (VAS)	√	√	√	√	√	
Thyroid tenderness	√	√	√	√	√	
Temperature monitor	√	√	√	√	√	
CRP and ESR	√		√		√	
Thyroid function	√				√	√
24 h I-131 uptake or thyroid scintigraphy	√					
Hematology panel	√				√	
Liver function	√				√	
Creatinine, uric acid	√				√	
Glucose	√				√	
AEs		√	√	√	√	√

*AE* adverse event, *CRP* C-reactive protein, *ESR* erythrocyte sedimentation rate, *VAS* visual analog scale

*The patients will receive face-to-face daily visit within the first week in research centers; thyroid pain, temperature, and AEs will be assessed at each visit

About 50% of patients have an initial thyrotoxic phase due to unregulated release of performed thyroid hormones from damaged thyroid follicular cells [3]. The thyrotoxic phase usually lasts 3–6 weeks, ending when the thyroid stores of preformed hormones are depleted. About 30% of patients subsequently enter a hypothyroid phase that can last up to 6 months. In the present study, anti-thyroid drugs will have no role and beta-blockers will be used as needed to control thyrotoxic symptoms. Levothyroxine will be employed when patients have a TSH level above 10 mIU/L or symptoms during the hypothyroid stage. In addition, although viral infection is regarded as the possible cause of SAT, antiviral medications will not be suggested in the study.

After the discontinuation of PSL, patients will be invited to participate in the following observational study in which a 3-month face-to-face visit will be planed. The details of the follow-up study will be described elsewhere.

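### The failure rules speak of termination without keeping patients in follow-up, and the 2-week rule applies to the 15 mg arm only, so primary-outcome days may be lost unevenly

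*Protocol article*

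**What the plan says.** The Treatment period section of the protocol article holds two rules for patients who do not respond.

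- **2-week rule, 15 mg arm only:** "if the test group still has pain at 2 weeks, consider termination, adjust to the standard initial dose for treatment". Patients whose pain cleared and came back are exempt ("with the exception of the situation that the pain completely disappears but the symptoms recur subsequently"). No counterpart is given for the 30 mg arm, where the taper simply waits until pain has resolved.
- **3-day rule, both arms** ("whether in the low initial dose or in the standard initial dose group"): if pain has not eased clearly and other causes are ruled out, "the study can be considered to be terminated, and the low initial dose can be adjusted to the standard initial dose". A 30 mg patient may go up to, for example, 40 mg.

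The same section provides for data collection in general terms: "During each telephone visit, thyroid pain, temperature, and AEs will be investigated, medicine usage will be directed and recorded". After a few pain-free days on the minimum dose, "discontinuation of PSL will be considered and patients will receive a face-to-face visit". It does not say whether these contacts continue for a patient terminated under either rule.

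Under Outcomes, the primary endpoint is total days on PSL, including re-treatment for recurrence. Under Statistical methods, the main analysis uses the full analysis set. A per-protocol analysis is added, and last observation carried forward is named for supportive sensitivity analyses.

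**The concern.** The endpoint is a duration of treatment, so a patient who fails 15 mg and moves to 30 mg adds outcome days after the switch. In the 3-day rule, terminating the study is listed alongside the dose change as a separate act, so a site could reasonably take termination to mean leaving the trial. Sites know the allocation and the decision is left to them.

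On that reading, days after the switch are never recorded, and no choice of analysis set can restore them. Losses under the 3-day rule can occur in both arms. Losses under the 2-week rule can occur only at 15 mg, the arm whose non-inferiority is to be shown. The risk to the conclusion is a non-inferiority claim that comes too easily.

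**Working it through.** **1. Plan's own figure.** Sample size estimate gives margin 7 days, SD 12, one-sided 5%, 38 per arm, 81% power. The normal approximation gives 81.5% and the noncentral t 80.9%. The stated figure reproduces.

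**2. Course lengths from the Treatment period section.** The 15 mg phase lasts 14 days, then "the dosage will then taper by 5 mg every 7–14 days over 2–4 weeks or longer". For the higher dose, "30 mg daily of PSL will be provided for around 5–14 days in the standard initial PSL dosage group", with a taper of the same overall length.

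- Unswitched 15 mg course: 14 + (14 to 28) = 28 to 42 days.
- Course switched at 2 weeks: 14 + (5 to 14) + (14 to 28) = 33 to 56 days.
- With equal taper length, a switched course is 5 to 14 days longer.

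**3. Assumptions.** The true 15 mg mean is 43 days and the 30 mg mean 36, so the excess equals the margin and any non-inferiority claim is false. Total SD is 12 per arm, with 38 or 45 per arm. A share p of the 15 mg arm is affected: 2%, 5% or 10%, about 1, 2 or 4 to 5 patients. The article gives no failure rate. Affected courses average D = 33, 43 or 56 days, with the arm mean held at 43.

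**4. Shift in the 15 mg mean.**

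- *Recorded as 14 days:* fall = p × (D − 14) = p × (19 to 42). This is 0.4 to 0.8 days at 2%, 0.95 to 2.1 at 5% and 1.9 to 4.2 at 10%. At 10% it is 1.9/7 = 27% to 4.2/7 = 60% of the margin.
- *Excluded:* the remaining mean is (43 − pD)/(1 − p). At p = 10% and D = 56 it is (43 − 5.6)/0.9 = 41.6, a fall of 1.4 days. At D = 33 it is (43 − 3.3)/0.9 = 44.1, a rise. Exclusion favours 15 mg only when affected courses run longer than the arm mean.

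**5. Simulated false non-inferiority rate** (pooled one-sided t-test, 40,000 to 60,000 runs per cell; ranges cover D and both sample sizes).

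| Handling | p = 2% | p = 5% | p = 10% |
|---|---|---|---|
| All PSL days counted | about 5% | about 5% | about 5% |
| Excluded, D = 33 to 56 | 4–6% | 3–8% | 2–14% |
| Excluded, equal taper (5 to 14 days longer) | about 6% | 6–8% | 7–14% |
| Recorded as 14 days | 6–9% | 9–19% | 15–46% |

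**6. Both rules together.** Let 5% to 10% of both arms be lost under the 3-day rule, with courses at the arm mean or 10 days above it.

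| Extra 2-week loss at 15 mg | Excluded | Recorded as 3 or 14 days |
|---|---|---|
| none | 5% | 6–7% |
| 5% | 3–10% | 10–21% |
| 10% | 2–17% | 15–44% |

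The balanced 3-day losses alone do little. The one-sided 2-week rule drives the result.

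**The case against.** The strongest reply is that this is silence in a condensed article, and that the text leans to the harmless reading. Each mention of termination is tied to further PSL dosing with the reason documented. Calls record medicine use, and the schedule places a visit at PSL discontinuation rather than at the end of the assigned dose. The endpoint is not limited to the assigned dose, and the full analysis set is primary. The asymmetry also has a clinical basis, because moving to the standard dose means nothing for a patient already on it.

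The size is open to challenge as well. The failure shares are assumed, and the article expects most patients to be pain-free within 5 to 10 days. Nothing prescribes 14-day scoring in the primary analysis. With affected courses at 33 days and the arm mean at 43, failures would finish sooner than successes, which is implausible.

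Much of this stands. The bias is not established, its direction under exclusion is not fixed, and the equal-taper row is the more plausible version of exclusion. What does not stand is that this is mere missing detail. The article states a rule that uses the word termination, addresses it to unblinded sites and lets it act on the primary endpoint. None of the mitigating text says that follow-up continues after termination. The fixed 14-day phase explains why a decision falls at day 14 in that arm, but not why the wording should leave doubt about staying in the study.

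**Conclusion.** The concern holds as a cheap improvement, with medium confidence. The wording allows a reading under which primary-outcome days of treatment failures go uncollected, and under the 2-week rule that loss is confined to 15 mg.

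If all days are collected and counted, the error rate stays at about 5% and there is no problem. If affected patients are dropped, the rate lies between 2% and 14% for the 2-week rule alone, and above 5% when a switched course is longer than an unswitched one. If their course is cut at 14 days, it lies between 6% and 46%. These rates rest on a true excess of exactly 7 days, SD 12 and 2% to 10% of the 15 mg arm affected. They describe analyses that drop or truncate these patients, not a full analysis set that counts every day.

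**What to change.** Add a few sentences to the Treatment period section:

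- Stopping or switching the assigned dose under the 2-week or 3-day rule is not withdrawal from the study.
- Every randomised patient in both arms is followed to final PSL discontinuation, through the calls and discontinuation visit already planned.
- In the full analysis set, all PSL days at any dose count in the randomised arm.
- Switches and escalations are reported by arm.

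The rescue rule, sample size and power stay as they are. The cost is the wording plus contacts already scheduled for about 1 to 5 of 45 patients at the assumed 2% to 10%. The downside for the sponsor is that low-dose durations may look longer, but those days belong to the endpoint as defined. Trial status describes recruitment as still open, so a clarification to sites could protect data not yet collected.
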